### Power analysis

The HRF features and dynamic glutamate changes associated with a cognitive task in individuals with fatigue and ME/CFS will be tested for the first time. Therefore, there are no preliminary results on these two groups' variances and means of these measures. This study's total sample size (*N* = 288) was determined to detect the effect size of 0.25 (Figure 4). For the same reason, the learning curve for neuromarker identification cannot be determined. However, one previous study determined that a test sample size of 100 would be needed to test a classifier to achieve reasonable precision in the validation (38).

**Figure 4 F4:**
[figure not shown]
Power analysis. The theoretic sample size was determined by the sensitivity value (effect size = 0.25) that further decreasing the effect size from 0.25 to 0.2 requires appreciably increasing the sample size from 251 to 390. The sample size assumes that 87% of data are valid (*N* = 251/0.87 ~ 288). Invalid data include MRI images with excessive motions and new conditions found after completion of the study, and the percentage was estimated empirically. The analysis of covariance (ANCOVA) will be used to determine the mean difference among four groups with 5 covariates of age, gender, activity levels, body mass index, depression, and anxiety. We assumed both type I and II errors of 0.05.

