### Data analysis plan

The measured variables will firstly be tested for normal distribution. Equivalent non-parametric methods will be used if any variable does not exhibit a normal distribution. The activity measure, body mass index, age, depression, and anxiety will be included as covariates for all statistical analyses. The false discovery rate (FDR) will be used to correct for multiple comparisons.

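### The stated sample sizes of 251 and 390 match a three-group test; for the planned four-group ANCOVA, 251 valid participants give 92.5% power at f = 0.25, not 95%

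*Protocol article*

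**What the plan says.** The Power analysis section sets the total of 288 to detect an effect size of 0.25 and refers to Figure 4 for the derivation. The legend of that figure supplies the inputs:

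- Choice of effect size: "further decreasing the effect size from 0.25 to 0.2 requires appreciably increasing the sample size from 251 to 390".
- Test: the ANCOVA "will be used to determine the mean difference among four groups".
- Error rates: "We assumed both type I and II errors of 0.05".
- Covariates: "5 covariates of age, gender, activity levels, body mass index, depression, and anxiety". The count is five, but six are named.
- Inflation: 87% of data are taken as valid, so 251/0.87 gives about 288.

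The analysis sections for Aim 1 and Aim 2 both plan a comparison across all four groups. On multiplicity, the Data analysis plan says: "The false discovery rate (FDR) will be used to correct for multiple comparisons".

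**The concern.** The legend gives enough to recompute the sample size, and the recomputed figure for four groups is not 251. If the number of groups was entered wrongly, the study does not have the 5% type II error that it claims for its main group comparison. Both figures in the pair that justifies stopping at 0.25 would also be wrong. The article says that it reports its analysis plans to improve reproducibility, so readers can be expected to rely on the printed figures.

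**Working it through.** **Inputs.** Alpha 0.05 and power 0.95, effect sizes 0.25 and 0.20, four groups, and five or six covariates, all from the Figure 4 legend. The effect size is read as Cohen's f. The article does not name the metric, but the exact match below supports that reading.

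**Method.** Fixed-effects ANCOVA with k groups and c covariates: df1 = k − 1, df2 = N − k − c, noncentrality λ = N·f². Power is the probability that a noncentral F(df1, df2, λ) exceeds the upper 5% point of the central F(df1, df2). The required N is the smallest with power of at least 0.95.

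**Step 1: reproduce the stated figures.**

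| Groups (df1) | N at f = 0.25 | N at f = 0.20 |
|---|---|---|
| 2 (1) | 210 | 327 |
| 3 (2) | **251** | **390** |
| 4 (3) | **279** | **434** |
| 5 (4) | 302–303 | 470 |

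The two-, three- and four-group rows are the same with 0, 5 or 6 covariates. The three-group row matches to the participant: at f = 0.25, N = 250 gives 94.98% and N = 251 gives 95.06%; at f = 0.20, N = 389 gives 94.99% and N = 390 gives 95.04%. With four groups and five covariates, no combination of alpha 0.01, 0.025, 0.05 or 0.10 with power 0.80, 0.90 or 0.95 gives the pair 251/390.

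**Step 2: power of the stated N in the stated design.** For N = 251, k = 4, c = 6 and f = 0.25:

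- λ = 251 × 0.25² = 15.69
- df1 = 3, df2 = 251 − 4 − 6 = 241, critical F = 2.64
- power = 0.925, so the type II error is 0.075 against the stated 0.05

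N = 390 at f = 0.20 also gives 0.925.

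**Step 3: what 251 does deliver at 95%.** Solving for f at N = 251 and k = 4 gives f = 0.264.

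**Step 4: what 95% at f = 0.25 would need.** 279 valid participants; 279/0.87 = 320.7, so about 321 enrolled. The inflation step in the legend is itself sound: 251/0.87 = 288.5.

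**Step 5: sensitivity to the valid share.** If all 288 were valid, power at f = 0.25 would be 95.7%. Reaching 279 valid out of 288 would take 279/288 = 96.9% valid data, against the 87% assumed.

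**Step 6: multiplicity, direction only.** The calculation is for one test at alpha 0.05. The HRF features are region-based, and the Data analysis plan applies an FDR correction. With FDR controlled at 5% (an assumed level; none is stated), no test in the family faces a threshold looser than 0.05, so 92.5% is a ceiling at f = 0.25. For illustration, single-test power at N = 251 is 87.6% at a threshold of 0.025, 79.5% at 0.01 and 54.6% at 0.001. The article does not say which threshold would apply.

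**The case against.** The strongest reply is that little turns on this. Power falls by 2.5 points and stays above 90%. The value 0.25 is not presented as a minimum important difference; it was chosen because going lower would cost many more participants. That reasoning survives correction, since 279 to 434 is about the same proportional step as 251 to 390 (434/279 = 1.56; 390/251 = 1.55). The shortfall also depends on an empirical valid share of 87%. All of this stands, and it is why the point is a reporting correction rather than a design failure.

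Two stronger readings are tempting. The first is that the regional HRF tests are badly underpowered once FDR is applied. A reader can produce low power figures by assuming a procedure, a level, a share of truly non-null regions and a uniform effect of 0.25. The article gives none of these, and it does not claim 95% power per region after adjustment. Only the direction of the loss is supported, and detail on the FDR family may properly sit in a fuller document.

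The second is that a null HRF result would be misread. The article sets no rule for interpreting null results, and a type II error of 0.075 instead of 0.05 would hardly change how one is read.

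Finally, the article does not report the df that was entered. Three groups is a strong inference from two exact matches, not a documented fact. The finding does not depend on it: whatever the cause, 251 does not give 95% power for four groups.

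**Conclusion.** The stated sample sizes are wrong for the stated design, and nothing elsewhere in the article repairs them. For one unadjusted four-group ANCOVA at alpha 0.05, 251 valid participants give 92.5% power at f = 0.25, and the effect detectable at 95% power is f = 0.264. The correct counterparts of 251 and 390 are 279 and 434. This rests on reading the effect size as Cohen's f and on 87% of data being valid. It does not depend on the covariate count, so naming six covariates while counting five is a minor slip with no effect on N. Unequal group sizes do not alter the result when f is defined with group weights. Severity: a should-fix reporting correction.

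**What to change.** Keep N = 288 and amend the Power analysis section and the Figure 4 legend:

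1. State that 251 valid participants in four groups give 92.5% power at f = 0.25, or 95% power at f = 0.264, for a single unadjusted test at alpha 0.05.
2. Replace 251 and 390 by 279 and 434 where the choice of 0.25 is explained, and make clear that 251 is the valid number expected from 288 at 87%, not the number required for 95% power.
3. Correct the covariate count from five to six.
4. Optionally, add one sentence noting that power for FDR-adjusted regional tests cannot exceed the single-test figure.

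The cost is wording only: no extra participants and no change to the analysis, with a slightly less favourable power claim. If the sponsor prefers to keep 95% at f = 0.25, the alternative is to enrol about 321, which is 33 more than planned (321 − 288).

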## Introduction

Myalgic encephalomyelitis/chronic fatigue syndrome (ME/CFS) is a serious, long-term illness for which the underlying disease process remains unknown, and no objective diagnostic test exists. The disease is characterized by profound fatigue for more than 6 months, cognitive and motor dysfunction, unrefreshing sleep, and/or orthostatic intolerance (1). There are 17 to 24 million people affected by ME/CFS, with 25% of them housebound (2). In addition to enduring the disease itself and its economic burden, 80% of ME/CFS patients struggle to get a diagnosis and are often left depressed by the lack of a diagnostic certainty and medical understanding of the disease processes. Although the etiology of ME/CFS remains unresolved, the well-documented autonomic dysfunction, sleep disturbance, cognitive impairments, altered sensory and pain perception, and reduced motor speed suggest that abnormal brain function plays a crucial role in the underlying disease process of ME/CFS (3). As such, ME/CFS has been classified as a neurological disease (ICD code 10 G93.3) by the WHO.

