### The recruitment and selection of the sample population

We will recruit 288 adult participants (18–65 years old), including 91 patients with ME/CFS, 61 individuals with chronic fatigue, 91 HCs with sedentary lifestyles, and 45 patients with fibromyalgia. The risk of an ill-defined ME/CFS patient cohort will be mitigated by employing a consensus diagnosis of ME/CFS from two clinicians ([name] and [name], both have over 10 years of experience in ME/CFS) and using the Canadian Consensus Criteria (CCC) 2003 (1). This study will also include groups of fibromyalgia, a frequent co-morbidity of ME/CFS. The American College of Rheumatology (ACR) 2016 fibromyalgia criteria (25) will be used for screening and followed by clinic diagnosis by a rheumatologist ([name]). The chronic fatigue is defined as self-identified ME/CFS but not confirmed by the two clinicians (i.e., present with other conditions or lack core ME/CFS symptoms) or with other disorders (not ME/CFS or fibromyalgia) that fatigue is a significant symptom. These two groups are included to ensure specificity of the identified neuromarker. Patients with ME/CFS have reduced daily activity because of their illness. However, a sedentary lifestyle itself may affect brain structure and function. Therefore, there is a risk of identifying brain structural or functional differences from ME/CFS sequelae, rather than from the illness per se. This study will mitigate against this problem by selecting HCs with sedentary lifestyles. A sedentary lifestyle will be defined as spending <60 min in moderate or high-intensity activity (i.e., exercise) per week (26). Furthermore, activity level will be monitored by the Actigraph GT3X-BT device (ActiGraph LLC., United States) for 14 days. The recorded activity level will be included as covariates for all statistical analyses but will not change participants' eligibility.

The inclusion criteria include adult individuals who express an interest, meet each group definition, and are confirmed by clinicians.

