The exclusion criteria include individuals (1) out of the age range, (2) pregnant, (3) with severe intellectual or mental impairment preventing them from fully understanding the study to give consent, (4) with mental disorders including post-traumatic stress disorder, obsessive compulsive disorder, schizophrenia, and bipolar disorder, (5) with a known other neurological disorder, (6) who cannot read and communicate in English, (7) recruited by supervising relationship or where a conflict of interest exists, (8) with alcohol or substance related disorder, (9) with BMI >35, (10) smoking (including marijuana or substance usage), (11) with diabetes, hypertension, or uncontrolled hyperlipidaemia, (12) currently on medication acting on the brain, (13) with a clinical diagnosis of hemochromatosis, (14) with a double copy of the Haemochromatosis gene, (15) who experienced migraines more than six times a year before the onset of their symptoms. A researcher will check the exclusion criteria at the screening stage. After the screening process, a differential diagnostic list will be completed by each participant and discussed with two clinicians for diagnosis of ME/CFS during clinical interviews.

Additional exclusion criteria for HCs include individuals (1) with a chronic disease, i.e., a condition that last 1 year or more and require ongoing medical attention or limit activities of daily living or both, including heart disease, stroke, lung cancer, colorectal cancer, depression, type 2 diabetes, arthritis, osteoporosis, asthma, chronic obstructive pulmonary disease, chronic kidney disease, and (2) who experience migraines more than six times a year, and (3) who do more than 60 min in moderate or high-intensity activity per week.

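### The stated 95% power for the four-group ANCOVA comes from a three-group calculation and makes no allowance for covariates related to group

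*Protocol article*

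**What the plan says.** The Power analysis section states: "This study's total sample size (*N* = 288) was determined to detect the effect size of 0.25". The Figure 4 legend adds "We assumed both type I and II errors of 0.05", so the intended power is 95%, and explains the choice of effect size: "further decreasing the effect size from 0.25 to 0.2 requires appreciably increasing the sample size from 251 to 390". The 251 is divided by 0.87 to allow for invalid data, which gives 288. The legend names the test: "The analysis of covariance (ANCOVA) will be used to determine the mean difference among four groups with 5 covariates of age, gender, activity levels", followed by body mass index, depression and anxiety. Neither place says whether 0.25 is a partial effect, a spread of adjusted means or a spread of unadjusted means.

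Other sections link some covariates to group:

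- **Activity.** The recruitment section says: "Patients with ME/CFS have reduced daily activity because of their illness". As a countermeasure it restricts healthy controls to people with under 60 minutes of moderate or intense activity per week.
- **Depression.** The additional exclusions for healthy controls list chronic conditions "including heart disease, stroke, lung cancer, colorectal cancer, depression" among them. The Introduction says that ME/CFS patients "are often left depressed by the lack of a diagnostic certainty".
- **Anxiety.** No section says how it differs by group.

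The data analysis plan puts activity, depression and anxiety into every analysis.

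**The concern.** In a randomised trial, covariates are balanced across groups in expectation, and adjusting for them costs little more than a few denominator degrees of freedom. Here the groups are diagnoses. If a covariate differs between groups, part of the group effect cannot be told apart from it, and the adjusted comparison carries less information than N × f² assumes. The tests for Aims 1 and 2 are these adjusted comparisons. If the 5% type II error does not belong to them, a null adjusted result would be read as stronger evidence of no difference than it is.

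**Working it through.** **Inputs from the article.** f = 0.25 (0.20 as the alternative), α = 0.05, power 0.95, 251 valid, four groups planned at 91/61/91/45. The legend counts "5 covariates of age, gender, activity levels, body mass index, depression, and anxiety", but lists six. I use six; five gives the same N. Valid numbers are taken as 79/53/79/40 (87% of plan, fibromyalgia rounded up so that the total is 251).

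**Step 1: reproduce the plan.** Noncentral F with λ = N × f² and denominator df = N − 4 − 6.

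| Numerator df | N at f = 0.25 | N at f = 0.20 |
|---|---|---|
| 2 (three groups) | 251 | 390 |
| 3 (four groups) | 279 | 434 |

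The printed 251 and 390 match numerator df 2 exactly. No overlap term is needed to obtain them, so none was used.

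**Step 2: correct the df only.** λ = 251 × 0.0625 = 15.69. With F(3, 241), power is 92.5%. So about 2.5 points of the shortfall from 95% have nothing to do with covariates.

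**Step 3: add overlap.** Multiply λ by the fraction of the group effect left after projecting out the covariates. The article gives no group-covariate association, so the following is assumed: all three patient groups are shifted from controls by d within-group SD, in the direction of more depression and less activity; the two covariates are uncorrelated within group, so D² = 2d²; f refers to the spread of adjusted means in residual-SD units.

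If the outcome differs between all patients and controls, with p = 79/251 = 0.3147 and p(1 − p) = 0.2157:

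retained = 1 / [1 + D² × 0.2157 × 251/247]

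If the outcome differs only between ME/CFS and the rest, the loss is multiplied by the squared correlation of the two group indicators, (79/172)² = 0.211.

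| d | D² | Retained, all patients differ | λ | Power | Retained, only ME/CFS differs | Power |
|---|---|---|---|---|---|---|
| 0.5 | 0.50 | 0.901 | 14.14 | 89.4% | 0.979 | 91.9% |
| 0.8 | 1.28 | 0.781 | 12.25 | 84.2% | 0.954 | 91.2% |
| 1.0 | 2.00 | 0.695 | 10.91 | 79.3% | 0.936 | 90.6% |

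Adding anxiety with the same shift and a 0.5 correlation with depression (also assumed) gives D² = 2.333d². The ranges become about 89% to 77% and about 92% to 90%.

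Overlap alone, on the plan's own numerator df of 2, takes 95.1% to 92.7%, 88.6% and 84.5% in the all-patients case.

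The low-loss case needs outcome and covariates to follow different patterns. If both are shifted in ME/CFS only, the retained fractions return to 0.901, 0.781 and 0.695, because the ME/CFS and control groups are the same size.

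**Step 4: the pairwise contrast.** The variance of the adjusted ME/CFS-minus-control difference is proportional to 1/79 + 1/79 + D²/241. Relative to 2/79 it rises by 8% at D² = 0.5, 16% at 1, 33% at 2 and 49% at 3.

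**Step 5: detectable effect.** At 251 with numerator df 3, the f detectable with 95% power is 0.264/√retained: 0.264 with no overlap, 0.278 at 0.901 and 0.316 at 0.695.

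**The case against.** The strongest reply is that 0.25 was never derived from group means. The Power analysis section says that none were available, and the legend picks it as a sensitivity value for an ANCOVA. If f is a partial effect, meaning variance explained by group after the covariates relative to residual variance, then λ = N × f² already reflects the overlap and nothing further is lost. That stands, but the article does not say so, and it does not rescue the 95%, because the four-group test still has 92.5%. Calling f adjusted is not enough: if it is the spread of adjusted means in residual-SD units, overlap still inflates the variance of the adjusted differences.

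A second reply is that covariates which explain outcome variance raise power. This counts only if f is in unadjusted SD units. Then, taking the size of the group differences as unchanged by adjustment, explaining about 10% of within-group variance (1 − 0.901) would cancel the overlap loss at d = 0.5, and about 30% (1 − 0.695) at d = 1. On that reading the net direction cannot be settled from the article.

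Third, the separation is partly undocumented. Sedentary controls narrow the activity gap. Brain-acting medication excludes people from every group, which may narrow the depression gap. The remark on depressed patients is background, not a description of this sample. All of this stands and limits the size of the point.

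**Conclusion.** The concern holds in a limited form. The 251 is the answer for a three-group test with covariates unrelated to group, whereas the planned test has four groups and covariates that the article itself ties to group in two cases. The df correction to 92.5% needs no assumption about covariates. The further drop, to about 89% to 79% if all patient groups differ from controls and about 92% to 91% if only ME/CFS does, rests on assumed shifts of 0.5 to 1 SD on depression and activity, and on f not being a partial effect.

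A reader might infer that activity, depression and anxiety all clearly separate patients from controls, that the adjusted test is therefore certainly weaker, and that the whole gap to 95% is due to covariates. The article does not support this. It is silent on anxiety by group, it reduces the activity gap by design, it leaves f undefined, and 2.5 points of the gap come from the df.

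**What to change.** In the Power analysis section and the Figure 4 legend:

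- Recompute with numerator df 3.
- State whether 0.25 is a partial, adjusted-mean or unadjusted effect.
- If it is not partial, estimate the group-covariate overlap from the 110 participants reported as recruited by 20 May 2022. This uses covariates and group only, with no imaging outcome.
- Report power at f = 0.25 and the detectable f over the resulting range. If f is in unadjusted SD units, also state the outcome variance that the covariates are assumed to explain.

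No extra participants and no change of analysis are needed. The cost is a short recalculation and a somewhat less favourable stated power.

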## Discussion

To the best of our knowledge, this is the first large-scale (*N* = 288) multimodal MRI study of ME/CFS worldwide. While preliminary studies with a small sample size have shed some light on potential mechanisms of and factors associated with ME/CFS, a large scale study with well-established methodological principles is required for decisive conclusions (23), which is more critical for ME/CFS because of the controversy associated with this ill-defined disease (24). The recommendation for improving reproducibility, fully reporting analysis plans to reduce the file-drawer effect (23), has culminated in this protocol paper.

### Controlling confounding factors

ME/CFS is an illness currently defined by consensus criteria and questionnaires completed by patients. Thus, there is a risk of an ill-defined ME/CFS patient cohort. The proposed study will mitigate this problem by following CCC ME/CFS criteria and diagnosis agreed by two experienced clinicians ([name] and [name]).

Patients with ME/CFS or fibromyalgia may have ongoing medications, which is logistically unavoidable for the study. We mitigate this risk by following steps. (1) Individuals using marijuana or substance were excluded because their known alteration of brain structure and function. (2) Each medication will be determined individually by agreement of investigators ([name], [name] and [name]) on whether it affects the NVC. We include individuals on medication that does not affect the NVC. (3) Two clinicians ([name] and [name]) will assess individuals on medication affecting the NVC to determine if it is safe to stop medication for 3 weeks. Individuals considered safe to stop medication will further seek professional opinions from their caring physicians and then stop medication 2 weeks before and 1 week after MRI. We will exclude individuals who are at risk to stop medication affecting the NVC.

Both ME/CFS and fibromyalgia predominantly affect females (39). Thus, we may recruit more females than males. Indeed, our current sample includes 82% female and 18% male in all groups, including HCs. This unequal sex ratio risk cannot be avoided because of diseases' inherent features. We will include sex as a covariate in all statistical analyses.

This project started when the severe acute respiratory syndrome coronavirus 2 (SARS-CoV-2) occurred before the long Covid (post-acute sequelae of SARS-CoV-2 infection) was recognized. We decided to keep the study protocol and follow the CCC ME/CFS criteria while considering SAR-CoV-2 as an infection similar to other infections that occurred before the manifestation of ME/CFS.

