### The secondary outcomes

i To compare brain structural and functional differences and associations with symptoms among ME/CFS, fibromyalgia, chronic fatigue, and healthy controls (HCs).ii To establish *group* differences in high-frequency heart rate variability and associated fMRI signal changes in ME/CFS.iii To establish *group* objective sleep quality differences and associated brain structure and function differences in ME/CFS.iv To establish *group* differences in sleep measures and changes low- and high-frequency heart rate variability during awake and sleep before and after MRI scanning.v To establish the repeatability of fMRS measures.

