I Structural MRI (sMRI) using a T1-weighted magnetization prepared rapid gradient-echo sequence (MPRAGE): 208 slices, dimension 256 × 256, voxel size 1 mm × 1 mm × 1 mm, TR/TE 2,200/1.71 ms, flip angle 7°.II A set of resting-state fMRI (rsfMRI, 192 volumes) using a multiband EPI sequence: 108 slices, dimension 126 × 126, multiband = 4, dimension 138 × 138, 1.6 mm^3^ isotropic voxel, TR/TE 2,500/42 ms, flip angle 75°. Participant will be instructed to keep their eyes open with fixation of a cross for 8 min acquisition. Heart rate will be recorded simultaneously using pulse oximetry from the MRI scanner.III A set of task fMRI (tfMRI, 800 volumes) using a multiband EPI sequence (60 slices, multiband = 8, dimension 74 × 74, 3 mm^3^ isotropic voxels, TR/TE 800/33 ms, flip angle 65°) while participants perform a symbol digit modalities test (SDMT), which is widely used for cognitive evaluation of information processing speed. A semi-random design, which simultaneously achieves maximum estimation efficiency and detection power, (30) was used (Figure 2). The paradigm is incorporated into the scanner's fMRI sequence for general linear modeling of BOLD signal changes associated with tasks. Brain regions with BOLD signal changes associated tasks are used for voxel location of functional magnetic resonance spectroscopy (fMRS).IV A set of breath-holding fMRI (BH fMRI, 324 volumes) will be acquired using the same pulse sequence and parameters as tfMRI above. Participants perform 6 BH tasks; each BH task consists of 14.4 s (18 fMRI volumes) natural breath, 3 paced breathing (4.8 s each with 2.4 s breath in and out, respectively) of 14.4 s and a 14.4 s end-expiration breath-hold.V A set of fMRS using the HERMES (Hadamard Encoding and Reconstruction of MEGA-Edited Spectroscopy) acquisition method with TR/TE = 2,000/23 ms. The task paradigm is the same as the tfMRI paradigm (Figure 2), during which 16 and 5 measurements (averaged from 8 volumes per measurement) are collected for task and resting block, respectively. A single cuboid voxel, 20 mm (superior-inferior), 27 mm (anterior-posterior), and 12 mm (left-right), covering the left dorsal prefrontal cortex, is adjusted according to individual BOLD activation maps (Figure 3).VI A set of diffusion tensor images (DTI) using a multiband EPI sequence (72 slices, multiband factor 3, dimension = 114 × 114, voxel size 2 × 2 × 2 mm^3^, TR/TE = 4,500/123 ms; free diffusion mode, 96 diffusion directions, bipolar diffusion scheme with two diffusion weighting of b = 0 and b = 2,500, phase encoding direction = anterior to posterior). Six volumes of b = 0 with phase encoding direction in posterior to anterior are also collected for the eddy current correction.VII A final set of rsfMRI will be collected using the same setting as II.

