#### Actigraphy data

The metabolic equivalent of the task from the GT3X_BT watch will be averaged over 14 days as the activity measure for each participant. The sleep outputs of the GT3X-BT watch, including latency, efficiency, total time in bed, total sleep time, wake after sleep onset, number of awakenings, and averaged awakening time calculated using the Cole-Kripke algorithm (31), will be averaged as objective sleep measurements for each participant. The 24-h heart rate will be downloaded and averaged to generate low- (< 0.1 Hz) and high-frequency (> 0.2 Hz) during awake and sleep for each participant.

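### Drugs are screened only for an effect on neurovascular coupling, so retained drugs that act on heart rate can distort the between-group heart rate variability comparison

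*Protocol article*

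**What the plan says.** **Medication rule** (Discussion, Controlling confounding factors). Ongoing medication in ME/CFS and fibromyalgia is described as unavoidable. The investigators decide drug by drug whether it affects NVC. Drugs that do are stopped from 2 weeks before to 1 week after MRI, or the person is excluded. For the rest: "We include individuals on medication that does not affect the NVC".

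**Other medication criterion** (The recruitment and selection of the sample population, exclusion 12). People "currently on medication acting on the brain" are excluded.

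**Health of the groups** (same section). Healthy controls have an extra exclusion for chronic disease needing ongoing care, "including heart disease, stroke, lung cancer, colorectal cancer, depression, type 2 diabetes, arthritis, osteoporosis, asthma, chronic obstructive pulmonary disease" and chronic kidney disease. The chronic fatigue group takes in people whose self-identified ME/CFS was not confirmed, "or with other disorders (not ME/CFS or fibromyalgia) that fatigue is a significant symptom".

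**Outcome** (The secondary outcomes, ii). The study will establish group "differences in high-frequency heart rate variability and associated fMRI signal changes in ME/CFS".

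**Measurement.** Under Actigraphy data, "The 24-h heart rate will be downloaded and averaged to generate low"- and high-frequency values, awake and asleep. Under Multimodal MRI, for the resting-state scan, "Heart rate will be recorded simultaneously using pulse oximetry from the MRI scanner".

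**Adjustment** (Data analysis plan). "The activity measure, body mass index, age, depression, and anxiety will be included as covariates for all statistical analyses". The Discussion adds sex.

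**The concern.** The medication rule suits the imaging aims, which concern NVC. HRV is a different kind of outcome: a drug can leave NVC alone and still change heart rate or autonomic tone. Such a drug passes both screens and is not stopped, so it is in use when HRV is recorded.

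This would matter little if use were equal across groups, but the eligibility rules push it apart. Healthy controls may not have a chronic disease under ongoing care; patients may, subject to the 15 general exclusions. With no medication term among the covariates, the planned model cannot separate drug from disease. A difference in HRV level between patients and controls could then be read as autonomic abnormality of ME/CFS when part of it is pharmacological.

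**Working it through.** **Step 1: does any rule catch a heart-rate or autonomic drug?**

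| Rule | What it asks | Catches such a drug? |
|---|---|---|
| Drug-by-drug review | Effect on NVC | Only if also judged NVC-active |
| Exclusion 12 | Action on the brain | Only if brain-acting |
| Exclusion 11 | Hypertension, diabetes, uncontrolled hyperlipidaemia | Only when taken for those conditions |
| Extra exclusions for controls | Any chronic disease under ongoing care | Indirectly, in controls only |
| Covariates | Activity, BMI, age, sex, depression, anxiety | No |

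Heart disease, asthma and chronic obstructive pulmonary disease appear only in the controls' list. Postural orthostatic tachycardia syndrome (POTS) is assessed under Clinical interviews and is not an exclusion. So there is a route by which patients, but not controls, can be on such drugs.

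**Step 2: size.** The plan has no figure to reproduce here. The share of users and the drug effect below are assumptions.

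Inputs:
- Valid participants, using the 87% in Figure 4: 0.87 × (91 ME/CFS, 61 chronic fatigue, 91 controls, 45 fibromyalgia) = 79, 53, 79, 39; N = 250.
- Six covariates and four groups: denominator df = 250 − 4 − 6 = 240; numerator df = 3.
- No disease effect; nominal 5% test.

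Net shift d = share of users × drug shift in SD. If ME/CFS alone carries it, the noncentrality is λ = d² × 79 × 171/250 = 54.04 d². If all three patient groups carry it, λ is the same, because ME/CFS and controls have equal n. The rejection rate is the upper tail of the noncentral F(3, 240, λ) beyond the 5% critical value.

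| Share | Drug shift | d | λ | Rejection, all drugs one way | Rejection, 75/25 opposing (d halved) |
|---|---|---|---|---|---|
| 5% | 0.5 SD | 0.025 | 0.034 | 5.2% | 5.05% |
| 10% | 0.5 SD | 0.05 | 0.135 | 5.8% | 5.2% |
| 20% | 0.5 SD | 0.10 | 0.540 | 8.3% | 5.8% |
| 20% | 0.8 SD | 0.16 | 1.383 | 14.2% | 7.1% |
| 30% | 0.8 SD | 0.24 | 3.112 | 28.0% | 9.9% |

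With an even split of directions the mean shift is zero.

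A simulation without covariates, including the extra variance from mixing users and non-users (15,000 runs), gives 6.0%, 8.4%, 13.0% and 25.5% for the last four one-direction rows, and 5.3%, 5.7%, 7.3% and 9.5% for their 75/25 counterparts. The added variance trims the two largest figures slightly.

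**Step 3: when does it double the error rate?** A 10% rejection rate needs d = 0.121 SD. That is 0.121/0.5 = 24% of patients at 0.5 SD, or 0.121/0.8 = 15% at 0.8 SD.

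**Step 4: against the planned effect.** Cohen's f = √(λ/N). For d = 0.05, f = √(0.135/250) = 0.023; for d = 0.24, f = √(3.112/250) = 0.112. These are 9% and 45% of the planned 0.25.

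**The case against.** The best counter-case has four parts.

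- **It may belong in the analysis plan.** The rule sits in the Discussion and serves the NVC hypothesis, for which it is sound. A sensitivity analysis of a secondary outcome is ordinary SAP content, and a fixed covariate list does not forbid one. This has force, but the point is not a missing policy. The article states how medication confounding will be handled and fixes covariates for every analysis, and what it states does not protect one of its own outcomes.
- **The exposed drugs may be few.** A drug must shift HRV, not act on the brain, be judged NVC-neutral, and be taken by someone who passes the hypertension exclusion and the clinicians' differential diagnosis. Under Disentangling NVC the article ties calcium channels and global blood flow to NVC, so some vasoactive drugs would be stopped or lead to exclusion. This stands: no passage shows how many patients are on such drugs, and it limits the likely share.
- **The imbalance is clearest for chronic fatigue, not ME/CFS.** If only that group carries the shift, λ = d² × 53 × 197/250 = 41.76 d², and the five rates become 5.2%, 5.6%, 7.5%, 11.9% and 22.2%. The ME/CFS versus control contrast is then unbiased. This is fair, though the controls-only exclusions also permit medicated ME/CFS patients.
- **The magnitudes are assumed,** and use a nominal 5% although the plan applies false discovery rate correction. True; the table is a range, not an estimate.

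**Conclusion.** The concern holds, as a minor one. The medication rule is tied to NVC, the eligibility rules favour unequal drug use between patients and controls, and the stated adjustment has no medication term. A between-group difference in HRV level therefore cannot be attributed to ME/CFS without knowing who was on a heart-rate or autonomic drug.

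The reach is one secondary outcome (ii), plus any comparison of HRV levels under iv. A steadily taken drug largely cancels in the before/after change in iv, and Aims 1–3 are not implicated. The size rests wholly on assumed shares, shifts and directions: negligible at 5–10% of patients and 0.5 SD, a doubled error rate at a net shift of about 0.12 SD, and up to 28% at the extreme considered.

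**What to change.** In the drug-by-drug review that already takes place, also record whether each drug is expected to alter heart rate or autonomic tone. Repeat the HRV level comparison without participants on flagged, retained drugs. Use the result to qualify what is attributed to ME/CFS, not as a pass/fail rule. Eligibility and stopping rules stay as they are.

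The cost is one extra column and one repeated analysis, with some loss of precision in the restricted comparison. The ME/CFS versus control interval widens by √(1/m + 1/79) / √(2/79), where m is the number of ME/CFS participants left:

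| ME/CFS removed | m | 95% half-width | Widening |
|---|---|---|---|
| None | 79 | 0.313 SD | – |
| 5% | 75 | 0.318 SD | 1.3% |
| 10% | 71 | 0.322 SD | 2.8% |
| 20% | 63 | 0.333 SD | 6.2% |
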